## Abstract

**Background:**

Career experience is a valuable approach to stimulate students’ learning interest and reshape their understanding of career pathways. However, the interaction effects between implementers and experiencers, particularly the benefits of the implementers, remain poorly understood. Furthermore, the role of peer-assisted learning in enhancing the effectiveness of career experience activities has not been thoroughly explored. This study aims to evaluate the impact of student-led healthcare career experience activity on nursing students’ professional commitment, academic self-efficacy and learning burnout.

**Methods:**

This is the study protocol for an open-label, randomized stepped-wedge crossover trial. This study will be set in a medical vocational college in China and will include 110 nursing students, who will be randomly allocated (1:1:1) to one of three groups. In a sequential, stepped-wedge manner, the groups will cross over from control conditions (Waitlist and Observer) to the intervention, where they will lead a healthcare career experience activity. The primary outcome of professional commitment, as well as the secondary outcomes of academic self-efficacy and learning burnout, will be measured via self-reported questionnaires at baseline and three subsequent time points (after the 4th, 8th, and 12th activity sessions). Data will be analyzed using Generalized Estimating Equation (GEE) analysis.

**Conclusion:**

This protocol details a student-led healthcare career experience activity, grounded in Kolb’s Experiential Learning Theory and Life Cycle Theory, and designed to enhance nursing students’ professional commitment. This trial is expected to provide empirical evidence on the feasibility of this peer-assisted learning model applied in a student-led nursing educational scenario, which facilitates both peer-to-peer and near-peer interactions. Furthermore, the outcomes are expected to inform the future development of student-led educational strategies.

**Trial registration:**

This study is registered in Chinese Clinical Trial Registry (ChiCTR2300070880). https://www.chictr.org.cn/bin/project/edit?pid=195337

## 1. Introduction

In recent years, global nurse turnover rates have risen, particularly among newly graduated nurses [1]. This trend presents a key challenge to the stability of the nursing workforce [2]. Factors such as transition shock, burnout, and emotional exhaustion contribute to this issue, which was amplified after the COVID-19 pandemic [3,4]. As a result, controlling turnover has become a critical priority for nursing educators and managers. Studies confirm that professional commitment is a core predictor of turnover intention. Strengthening this commitment through early interventions during school is an effective strategy to reduce future turnover [5,6]. According to Career Construction Theory, career experience is an essential part of career development [7]. It serves as a form of social support and plays a vital role in enhancing students’ professional commitment [8,9].

As a dynamic and interactive process, career experience has been shown to spark learning interest, refine occupational perceptions, and enhance planning skills [10–15], However, traditional career experience models face two major challenges in practice. The first is a high dependency on resources. Traditional models often require qualified instructors and real clinical or campus venues [16–18]. This places significant pressure on institutional finances and human resources, making such activities difficult to sustain [19]. The second problem is the limited perspective of existing research. Previous studies have focused almost exclusively on the benefits for experiencers, while largely ignoring the effects on the activity implementers, such as medical staff or teachers [20,21]. This represents a significant research gap. To address these challenges, the peer-assisted learning (PAL) model offers a potential solution.

The core of PAL is that students acquire knowledge and skills through the active support of their peers [22]. The advantage of this model is transforming resource limitations into a teaching opportunity. By allowing students to act as facilitators, this approach greatly reduces the reliance on professional faculty. More importantly, it shifts students from being passive recipients of knowledge to active creators of it. In the process of teaching others, they can develop their leadership, communication, and organizational skills [23–25]. These are key competencies for their future careers that are difficult to achieve in traditional teacher-led models. Moreover, peer interaction can create a more equal learning environment [22]. This may help to increase student motivation and potentially reduce the learning burnout prevalent in nursing programs [26,27]. Previous studies show that student-led activities can effectively enhance professional identity [28–30]. Despite these advantages, the PAL model also faces its own challenges, such as a potential lack of student motivation or conflict within groups, as well as the need for structured training and resource support. All these factors must be considered in the design [31].

Therefore, this study aims to address the following research questions: (1) How was the student-led healthcare career experience activity developed? (2) How will the key outcomes (professional commitment, academic self-efficacy, and learning burnout) change across four measurement time points (T0-T3)? (3) What are the differences in outcomes between Group 1 at T1 and T2? (4) What are the differences in outcomes among all groups at T3?

## 2. Theoretical and conceptual model

The theoretical foundation for this study is Kolb’s Experiential Learning Theory [32]. It emphasizes that learners construct knowledge through the active transformation of experience. Experiential learning has been widely applied in nursing education to facilitate active learning and develop practical skills [33,34]. However, many of these applications remain teacher-led, focusing on students as passive recipients of pre-structured experiences. The potential for students to learn by actively creating and facilitating an experience for others, particularly in relation to their own professional identity and learning attitudes, remains underexplored.

To structure the content of the intervention, the Life Cycle Theory was utilized. Nursing roles were categorized according to three major life stages: juvenile, young and middle-aged, and elderly. This framework provides a comprehensive and relatable structure for demonstrating the critical role of nursing across a person’s entire lifespan.

These two theories were integrated to create the student-led activity. The Life Cycle Theory provided the structured content of the nursing stations. Kolb’s Experiential Learning Theory provided the process through which the nursing students, as implementers, would learn. For each station, the nursing students will guide experiencers through the four stages of experiential learning. Nursing students themselves will actively engage in a learning cycle by gaining concrete experience by leading the activities, observing experiencers’ reactions and reflecting on their teaching performance, and subsequently conceptualizing these insights to refine their understanding of their professional role. This process is designed to deepen their own understanding of nursing roles and enhance their professional commitment. As a secondary benefit, this activity also helps high school students understand the significance of nursing across the human life cycle (Fig 1).

**Fig 1 pone.0340372.g001:**
[figure not shown]
Conceptual framework of healthcare career experience activity.

## 3. Methods

### 3.1. Study design

This study will utilize an open-label, randomized, stepped-wedge crossover design. Eligible nursing students will be randomly assigned in a 1:1:1 ratio to one of three groups: Group 1 (Implementers+Followup+Followup) (IFF), 2 (Observers+Implementers+Followup) (OIF) or 3 (Waitlist+Observers+Implementers) (WOI). In accordance with the stepped-wedge schedule, all groups will sequentially receive the intervention after transitioning through control conditions (Observer or Waitlist). The specific sequence of roles and intervention timing for each group is detailed in Fig 2. Outcomes will be measured at four time points: baseline (T0), and at three subsequent follow-up points (T1, T2, T3). The schedule of enrollment, interventions, and assessments is shown in Fig 3. This stepped-wedge design was chosen for two main reasons. First, it allows all participants to eventually receive the intervention, which is ethically preferable in educational studies. Second, it helps to control for time-related confounding variables. This protocol is reported in accordance with the recommendations for clinical trials guidelines (SPIRIT) [35].

**Fig 2 pone.0340372.g002:**
[figure not shown]
The flowchart of student enrollment and group allocation.

**Fig 3 pone.0340372.g003:**
[figure not shown]
The schedule of enrollment, interventions, and assessments.

### 3.2. Ethics

This study protocol was approved by the Medical Ethics Review Committee of Quanzhou Medical College (No. 2023003). Prior to enrollment, all participants will receive detailed information about the study and will be required to provide both verbal and written informed consent. Participants will be informed of their right to withdraw from the study at any time without any negative consequences. All data, including participant growth files will be stored securely and confidentially in an archives room, in accordance with the guidelines of the Medical Ethics Review Committee of Quanzhou Medical College. Access to the dataset is restricted to the principal researchers involved in this study to ensure confidentiality.

### 3.3. Participants

#### 3.3.1. Nursing students.

Participants are second-year nursing students from the school of nursing at a medical vocational college in China. The study aims to include all eligible students from this cohort who volunteer to participate. The inclusion criteria are as follows: (1) full-time nursing who have completed at least one academic year of study; (2) recruited through the national college entrance examination; and (3) provided written informed consent after understanding the study details. The exclusion criteria are: (1) students who drop out; (2) students who are suspended from school; or (3) students who change their major during the study period.

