### 3.8. Outcomes and measures

#### 3.8.1. Main outcome: professional commitment.

The primary outcome measure in this study is the change in professional commitment among nursing students. This outcome will be measured using the Undergraduate Professional Commitment Scale, developed by Lian R et al [42]. The scale is organized into four dimensions: emotional commitment, continuing commitment, ideal commitment, and normative commitment. It comprises 27 items, with responses rated on a 5-point Likert scale ranging from 1 (“completely inconsistent”) to 5 (“completely consistent”). Higher scores indicate greater professional commitment. The scale demonstrates strong reliability, with a Cronbach’s α coefficient of 0.927.

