### 3.9. Statistical analysis

All statistical analyses will be performed using SPSS version 27.0. Demographic variables will be summarized using descriptive statistics. In accordance with the Intention-to-Treat (ITT) principle, all randomized participants will be included in the analysis. Missing data will be handled using the GEE model under the Missing at Random (MAR) assumption. The GEE model will be used to compare differences between and within groups, controlling for time effects and baseline scores of the outcome variables (professional commitment, academic self-efficacy, and learning burnout). To examine the specific impact of each intervention role, the Group variable will be analyzed as a three-level categorical factor (Implementer, Observer, Waitlist). The interaction effect between time and group allocation will also be examined. Post-hoc multiple comparisons between groups will be conducted using the Bonferroni correction. For all analyses, statistical significance is set at a p-value of < 0.05.

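### Exclusion criteria that can be met after randomisation conflict with the rule that every randomised student is analysed

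*Protocol article*

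**What the plan says.** Section 3.3.1 (Nursing students) requires at entry "full-time nursing who have completed at least one academic year of study". It then states: "The exclusion criteria are: (1) students who drop out; (2) students who are suspended from school", and adds as the third criterion "students who change their major during the study period".

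Section 3.9 (Statistical analysis) defines the analysis set: "In accordance with the Intention-to-Treat (ITT) principle, all randomized participants will be included in the analysis". It continues: "Missing data will be handled using the GEE model under the Missing at Random (MAR) assumption".

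Section 3.8.1 gives the endpoint: "The primary outcome measure in this study is the change in professional commitment among nursing students". The Introduction says of that construct: "Studies confirm that professional commitment is a core predictor of turnover intention". Under Limitations (section 5), the article accepts that a waitlist may cause withdrawal, with attrition or self-selection bias.

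No section says whether a student who meets one of the three criteria after allocation keeps a place in the analysis, or only stops taking part in the activity.

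**The concern.** An exclusion criterion decides who may enter a trial, so it should be checkable before randomisation. The third criterion is tied in its own words to the study period, which continues after allocation. The first has little meaning as a status at screening, since entry already requires full-time enrolment. Applied as written, they take out students who have been randomised, and section 3.9 rules that out. Two analysts following the article could build different primary analysis sets.

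The choice matters because leaving the nursing major is plausibly related to commitment to nursing, which is the primary outcome. Removal could also differ by group. Section 3.3.2 sets one session every two weeks, and section 3.6.2 has Groups 2 and 3 become implementers after the 4th and 8th sessions, so after about 8 and 16 weeks, while Group 1 starts at once. Everyone knows their group. If low scorers were removed mainly from the waiting groups, those groups' means would rise and a real benefit would be understated. Removal mainly from active implementers would overstate it.

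**Working it through.** **1. The two rules side by side.**

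| Event | Timing given in 3.3.1 | Could it be a status at screening? | Conflict with 3.9 if it occurs after allocation |
|---|---|---|---|
| Change of major | During the study period | Only for a change before allocation | Yes, explicit |
| Dropping out | None | Hardly, given the inclusion criterion | Yes, by sense |
| Suspension | None | Yes | Only if read as a later event |

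The conflict is certain for the first row, and that alone calls for a correction.

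**2. The plan's own figure.** Inputs from section 3.4: α 0.05 (taken as two-sided), power 0.80, δ = 0.50 SD, ρ = 0.35, m = 4 measurements. For a two-group comparison of averages over visits with exchangeable correlation:

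n = 2(z₀.₉₇₅ + z₀.₈₀)² [1 + (m − 1)ρ] / (m δ²) = 2(1.960 + 0.842)² × 2.05 / (4 × 0.25) = 32.18, so 33 per group. Then 3 × 33 = 99, and 99 / 0.90 = 110.

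Both stated figures reproduce. They do not depend on this point. The 0.50 SD is the yardstick below.

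**3. Size of the possible bias, simple model.** The documents give no removal rates and no correlation between leaving and the score, so both are assumptions. Suppose scores are normal, and the lowest fraction q of a group is removed on a trait that correlates r with the score. The group mean then rises by

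shift = r × φ(z_q) / (1 − q), in SD units.

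- q = 0.05: 0.1031 / 0.95 = 0.109
- q = 0.10: 0.1755 / 0.90 = 0.195
- q = 0.15: 0.2332 / 0.85 = 0.274

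| Removal | r = 0 | r = 0.5 | r = 1 |
|---|---|---|---|
| 10% in every group | 0 | 0 | 0 |
| 5% in one group, 15% in another | 0 | 0.083 | 0.166 |
| None in one group, 10% in another | 0 | 0.097 | 0.195 |

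Entries are spurious between-group differences in SD. The last row is about 20% and 39% of the planned 0.50 SD. With 110 / 3 ≈ 37 students per group, 10% of one group is about four students.

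**4. Closer to the planned analysis.** Section 3.9 adjusts for the baseline score and uses role (Implementer, Observer, Waitlist) as the factor. By Table 3, a removed Group 3 student loses records in all three roles, so part of the shift cancels. Simulation of that model with ρ = 0.35, no true effect and 10% removed from Group 3 only gave these Implementer–Waitlist biases:

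- removal on the stable level or on the mean follow-up score: about 0.06 to 0.15 SD at r = 1, and 0.03 to 0.08 SD at r = 0.5;
- removal on the T1 score itself at r = 1: 0.16 to 0.18 SD.

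The Implementer–Observer bias was at most about 0.07 SD. The simple model is therefore near an upper bound.

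**The case against.** The strongest reply is that section 3.9 is the only place that defines an analysis set, and it keeps everyone. Section 3.3.1 describes participants. It can be read as saying that such students stop taking part while their data stay in. On that reading the fault is loose wording, not a planned biased analysis. This stands in part: nowhere does the article say that data will be discarded, and a reader who infers a settled plan to delete them goes beyond the text. But it is only one way to resolve the conflict, and the article does not choose it.

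Second, recruitment runs from June 2025 to June 2026 into a volunteer pool (section 3.5.1). A volunteer could be suspended, leave or change major while in the pool and before allocation, and exclusion then would be harmless. This also stands. It is why the criticism cannot be that all three criteria are necessarily post-randomisation events.

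Third, a reader might infer that those removed are the students with the lowest commitment. The documents do not show this. The Introduction links commitment to turnover intention in a discussion of nurse turnover and does not address students who change major or are suspended. A tendency to low commitment is a strong inference for change of major, plausible for dropout, and weak for suspension.

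A last defence, that the missing-data approach covers the loss, does not hold. Students taken out of the analysis set are not missing data in the model. For those kept with missed visits, standard unweighted GEE is in general valid only when data are missing completely at random.

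**Conclusion.** The concern holds as a contradiction between two stated rules. It is explicit for change of major, follows by sense for dropout, and is possible for suspension. It is not a matter of detail left to an analysis plan, because an analysis plan could follow only one of the two rules and would leave the other wrong.

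The consequence is conditional. There is no between-group bias if removal is equal across groups or unrelated to the score. With 10% removed from one group only and r between 0.5 and 1, the bias is at most about 0.1 to 0.2 SD against the planned 0.50 SD, and probably less once baseline adjustment and the role-based analysis are counted. It would be tempting to conclude that the trial will lose up to 40% of its planned effect. The documents do not support that: it needs perfect selection, all of it in one group, and a simple parallel comparison. The reason to act is that the conflict decides who is in the primary analysis, and that questionnaires not collected from leavers cannot be recovered later.

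**What to change.** - In section 3.3.1, keep as eligibility criteria only facts known before randomisation, for example not being suspended at that date.
- List dropout, suspension and change of major after randomisation as reasons for discontinuing the activity.
- In section 3.9, state that these students stay in the ITT set in their randomised sequence with all data collected, and are asked for the remaining questionnaires where they consent.
- Report the number of each event by group.

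The cost is some rewording and a few extra questionnaires; the target of 33 per group and 110 in total stands. One drawback should be acknowledged: a professional-commitment score from someone who has left nursing may be harder to interpret, and students who withdraw need not answer.

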#### 3.3.2. Middle school students.

The experiencers for the activity will be recruited from a middle school near the medical vocational college. In collaboration with the school, the activity is held once every two weeks on weekends for students who volunteer to participate. To ensure a high-quality experience and due to venue limitations, each activity session is limited to a total of 18–36 experiencers. This group size is designed to be manageable and allows for the experiencers to be subsequently divided into three smaller teams for the different experiential modules.

### 3.4. Sample size

The sample size was estimated specifically for a GEE analysis using the longpower package in R statistical software (version 4.4.3). The calculation was designed to detect significant differences in the primary outcome among the three groups across four repeated measurement points. The parameters were set based on standard benchmarks: a significance level (α) of 0.05, a power of 0.80, and a standard medium effect size (δ = 0.50). Regarding the correlation structure, we adopted a conservative estimation. Given that professional commitment is a dynamic construct [36], we assumed a moderate within-subject correlation (ρ = 0.35) [37]. Based on these parameters, the minimum required sample size is 33 participants per group. To account for a potential 10% attrition rate, the final target sample size is set at 110 participants. This method of ensuring adequate statistical power aligns with recommendations in methodological literature [38,39].

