#### 3.6.2. Intervention.

**Intervention Timing Arrangement.** The intervention timing will follow the stepped-wedge design detailed previously (Fig 2). Group 1 (IFF) will initially act as the intervention group (implementers), while Group 2 (OIF) and Group 3 (WOI) will begin in control conditions as Observers and Waitlist, respectively. Subsequently, Group 2 and Group 3 will cross over to the implementer role after the 4th and 8th activity sessions, respectively. After completing four activity sessions, nursing students have the option to continue their participation in a subsequent volunteer pool. The specific roles for each group at each phase are outlined in Fig 2 and Fig 4.

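### The 33 per group and 80% power match a two-group formula with a constant 0.50 SD gap at all four visits; this stepped wedge has no such gap, so the 80% is not the power of the planned analysis

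*Protocol article*

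**What the plan says.** Section 3.4 gives its method as "The sample size was estimated specifically for a GEE analysis using the longpower package in R statistical software (version 4.4.3") and its purpose as follows: "The calculation was designed to detect significant differences in the primary outcome among the three groups across four repeated measurement points". The inputs are "a significance level (α) of 0.05, a power of 0.80, and a standard medium effect size (δ = 0.50"), and for the correlation "we assumed a moderate within-subject correlation (ρ = 0.35"). The result is that "the minimum required sample size is 33 participants per group", and then "To account for a potential 10% attrition rate, the final target sample size is set at 110 participants". The section lists no crossover schedule, time effects, role coding or multiplicity adjustment among the inputs.

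The design sections describe something other than parallel groups. Section 3.1 makes T0 a baseline and says that "all groups will sequentially receive the intervention". Section 3.6.2 sets the timing: "Group 2 and Group 3 will cross over to the implementer role after the 4th and 8th activity sessions, respectively". Section 3.9 plans a GEE that controls for time and baseline score, uses a role factor with three levels (Implementer, Observer, Waitlist), examines a time-by-group interaction, and applies Bonferroni to pairwise comparisons.

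**The concern.** A calculation for a repeated-measures mean difference divides the variance by the number of occasions at which the difference is present. Section 3.4 counts four occasions. In this trial the expected gap at T0 is zero by randomisation, and the groups' roles change at each later visit. No pair of groups, and no pair of roles, stays a fixed distance apart over T0 to T3.

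If the 80% belongs to no contrast that the trial will report, readers will misjudge its results. A null Implementer versus Waitlist result would be taken as negative with adequate power, when the chance of detecting 0.50 SD was nearer two in three, or below one in two after Bonferroni. A null comparison of groups at T3 (research question 4) would be misread in the same way.

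**Working it through.** **Inputs.** From section 3.4: α 0.05, power 0.80, δ 0.50 (SD = 1), ρ 0.35, four measurements, 33 per group, 10% attrition, 110 in total. My assumptions: two-sided test, exchangeable correlation, T0 untreated in all groups.

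**Step 1. Reproduce the stated figure.** For two groups with a constant difference over m visits:

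n per group = 2(z₀.₉₇₅ + z₀.₈₀)² [1 + (m − 1)ρ] / (m δ²)

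With (1.960 + 0.842)² = 7.849, m = 4, ρ = 0.35 and δ = 0.50:

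2 × 7.849 × 2.05 / (4 × 0.25) = 32.18, so 33. Then 3 × 33 = 99, and 99 / 0.90 = 110.

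Both stated figures are reproduced. Other variants are not close: one-sided with four visits gives 26, three visits 36, a single visit 63, α/3 with four visits 43, and three post-baseline visits adjusted for baseline 28.

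**Step 2. Set that formula against the schedule** (sections 3.1 and 3.6.2, Table 3).

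| Visit | Group 1 | Group 2 | Group 3 |
|---|---|---|---|
| T0 | untreated | untreated | untreated |
| T1 | Implementer | Observer | Waitlist |
| T2 | Follow-up | Implementer | Observer |
| T3 | Follow-up | Follow-up | Implementer |

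Implementer and Waitlist meet after baseline only at T1. By T3 all three groups have led.

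**Step 3. The formula's own quantity under this schedule.** Suppose leading adds a lasting 0.50 SD and observing adds nothing. The four-visit means are then 0.375, 0.25 and 0.125 SD for Groups 1, 2 and 3. The largest gap (Group 1 v Group 3) is 0.25 SD. The standard error is √(2 × 2.05 / (4 × 33)) = 0.176, so power is Φ(0.25/0.176 − 1.96) = 29%. Adjacent groups differ by 0.125 SD, with power 11%. At T3 the expected gap between groups is zero.

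**Step 4. The role model on the actual layout.** Take four time effects plus role effects, and V exchangeable with ρ. Then Var = c′[n Σ_g X_g′V⁻¹X_g]⁻¹c, and power = Φ(δ/SE − z). The table uses 33 per group and ρ = 0.35.

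| Contrast | SE | Power for 0.50 SD |
|---|---|---|
| Implementer v Waitlist, follow-up coded as Implementer | 0.2145 | 64% |
| Implementer v Waitlist, separate follow-up level | 0.2183 | 63% |
| The same two at α/3 (Bonferroni, three pairs) | as above | 47%, 46% |
| Implementer v Observer | 0.144–0.145 | 93% (41% if the gap is 0.25 SD) |
| Pooled two-level wedge, observing inert, effect lasting | 0.1409 | 94% |

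For Implementer v Waitlist the detectable difference at 80% is 2.80 × 0.2145 = 0.60 SD, or 2.80 × 0.2183 = 0.61 SD.

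**Step 5. Sensitivity of Implementer v Waitlist** (unadjusted α, both follow-up codings). With 33 per group:

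- ρ = 0.20: 59–60%
- ρ = 0.35: 63–64%
- ρ = 0.50: 70–73%
- ρ = 0.70: 86–89%

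With 110/3 = 36.67 per group (no attrition) and ρ = 0.35: 68–69%.

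The two calculations respond to ρ in opposite directions. In the Step 1 formula a higher ρ raises n (40 at ρ = 0.50); in the wedge a higher ρ raises power.

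**The case against.** Four points can be made for the plan.

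- **The arithmetic is right.** 33 and 110 both follow from the stated inputs. This stands: the fault is in design fit, and a reader should not infer a miscalculation.
- **The formula is not stated.** Section 3.4 names a package but no function, and an article may leave the call to a fuller document. This also stands in part. The exact match is strong evidence, not proof. But no calculation on the real schedule that I ran with these inputs returns 33, and the section presents its result as covering three groups over four visits.
- **The trial may not be underpowered.** A reader might infer that it is. The documents do not support that without qualification, because Implementer v Observer and the pooled wedge both exceed 80% on their own assumptions. Those assumptions are demanding, however. The Discussion treats observing as an active comparator, which argues against an inert Observer phase and against a full 0.50 SD gap between leading and observing.
- **Power could be quoted for a 0.50 SD gap at T3.** A single-visit figure can be computed, but it would mislead. Under a common lasting effect that gap is zero, and a T3 difference needs some further assumption, such as waning, that the article does not state.

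Table 3 prints the coming role against T0. Coding T0 that way would bring Implementer v Waitlist back to 79% (74% with a separate follow-up level), but only by counting an untreated baseline as treated.

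**Conclusion.** The concern holds as a mismatch between section 3.4 and the design and analysis in sections 3.1, 3.6.2 and 3.9. The stated 80% is not the power of the planned analysis. For 0.50 SD with 33 per group and ρ 0.35, power is about 63–64% for Implementer v Waitlist before Bonferroni and 46–47% after, 93% for Implementer v Observer, and 94% for a pooled wedge. Groups compared on their T0–T3 average have at most about 29% under a lasting 0.50 SD effect. The 80% does not cover research question 4, since no T3 difference is expected if the effect is common and lasting.

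These figures rest on exchangeable correlation, an untreated T0, a normal approximation and, for the pooled and averaged contrasts, a lasting effect. The direction of the discrepancy depends on the contrast. Because ρ is itself assumed, the values are a guide to size and should not be printed as fixed replacements.

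**What to change.** In section 3.4:

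1. Withdraw the statement that 33 per group gives 80% power.
2. Name the primary contrast.
3. Recompute power, or the detectable difference at 80%, for that contrast on the actual group-by-visit layout under the section 3.9 model. Include time effects, the role coding (with a statement of how follow-up periods are coded), and Bonferroni where it applies.
4. Show the result over a range of ρ, for example 0.20 to 0.70, for both 99 evaluable and 110 enrolled students.
5. State that research question 4 is not covered by this power unless a specific T3 difference is assumed and justified.

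The cost is one recalculation and a rewritten paragraph. The stated power becomes less favourable if Implementer v Waitlist is the primary contrast. No extra students, visits or change of design are requested.

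### The single 80% power figure does not fit the stepped-wedge layout: on the protocol's own inputs, Implementer versus Waitlist has about 58–65% power, and the overall role test depends on where Observer falls

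*Protocol article*

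**What the plan says.** Section 3.4 says the calculation was meant to "detect significant differences in the primary outcome among the three groups across four repeated measurement points". Its inputs are "a significance level (α) of 0.05, a power of 0.80", a standardised effect of 0.50 and a within-subject correlation of 0.35. On the correlation it adds: "Regarding the correlation structure, we adopted a conservative estimation". The result is that "the minimum required sample size is 33 participants per group", raised to 110 in total for 10% attrition. The R package is named; the function and the layout given to it are not.

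Sections 3.1, 3.6.2 and Table 3 set out the design. The four measurements are baseline (T0) and T1 to T3. Group 1 goes Implementer, Follow-up, Follow-up. Group 2 goes Observer, Implementer, Follow-up. Group 3 goes Waitlist, Observer, Implementer.

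Section 3.9 analyses role as a three-level factor (Implementer, Observer, Waitlist) by GEE, adjusts for time and baseline score, and states: "Post-hoc multiple comparisons between groups will be conducted using the Bonferroni correction".

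**The concern.** The stated inputs lead to 33 by a formula for two parallel arms that differ by the same amount at every visit. This trial has three groups, a pre-intervention measurement among the four, and roles that change each period. Waitlist is the only condition without exposure to the activity, since Observers watch it and the Discussion treats them as an active comparator. After baseline, Waitlist contributes one group at one visit.

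If the 80% is read as applying to every comparison among the three roles, a non-significant Implementer-versus-Waitlist result would carry more weight than the design gives it.

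**Working it through.** **Inputs.** From section 3.4: α 0.05, power 0.80, δ 0.50 (so SD = 1), ρ 0.35, four measurements, 33 per group. From section 3.9: adjustment for time and baseline, and Bonferroni, taken over three pairwise role comparisons (0.05/3 = 0.0167). Assumed: two-sided tests, exchangeable correlation, normal approximation.

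**1. Reproducing the plan's figure.** Two arms, constant difference, m visits:

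n = 2(z₀.₉₇₅ + z₀.₈₀)²[1 + (m − 1)ρ] / (mδ²)

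With m = 4: 2 × 7.849 × 2.05 / (4 × 0.25) = 32.18, so 33. Then 3 × 33 / 0.9 = 110. Both figures match. Among the variants tried, this is the only one that uses the stated four measurements and returns 33. A three-group test with means 0, 0 and 0.5 also gives 33, but only with three visits.

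**2. What counting T0 does.** The standard error in that formula at n = 33 is √(2 × 2.05 / (4 × 33)) = 0.176. A 0.5 SD difference at all four visits gives power Φ(0.5/0.176 − 1.960) = 81%. If T0 contributes no difference, the average is 3 × 0.5 / 4 = 0.375, and power is Φ(0.375/0.176 − 1.960) = 57%.

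**3. Implementer versus Waitlist at T1, adjusted for T0.** SE = √(2(1 − 0.35²)/33) = 0.231.
- At 0.05: Φ(0.5/0.231 − 1.960) = 58%.
- At 0.0167: Φ(0.5/0.231 − 2.394) = 41%.
- Effect detectable with 80% power: 2.802 × 0.231 = 0.65 SD.

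**4. Role model using all post-baseline visits.** This is generalised least squares with period effects and role effects. Given T0, each visit has variance 1 − 0.35² = 0.8775 and each pair of visits has covariance 0.35 − 0.35² = 0.2275. Section 3.9 lists three roles and does not place the Follow-up cells, so three codings were run. Entries are power for 0.5 SD at 33 per group, with the Bonferroni level in brackets.

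| Follow-up cells | SE, Implementer − Waitlist | Implementer v Waitlist | Effect for 80% power | Implementer v Observer |
|---|---|---|---|---|
| own level | 0.218 | 63% (46%) | 0.61 SD | 93% (86%) |
| dropped | 0.224 | 61% (44%) | 0.63 SD | 91% (81%) |
| counted as Implementer | 0.215 | 64% (47%) | 0.60 SD | 93% (86%) |

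A simulated GEE (T1–T3 outcomes, T0 as covariate, 1,500 runs) gave 65% (49%) for Implementer versus Waitlist. Its Monte Carlo standard error is about 1.2–1.3 percentage points, so it agrees with the table. With 36 analysed per group the role model gives 65–68% (48–52%).

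**5. The two-degree-of-freedom role test**, same layout, α 0.05, 33 per group, over the three codings:

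| Effect pattern (SD above Waitlist) | Power |
|---|---|
| Observer 0, Implementer 0.5 | 86–90% |
| Observer 0.25, Implementer 0.5 | 54–58% |
| Observer 0.5, Implementer 0.5 | 63–66% |

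**6. Direction of ρ.** The values above 0.35 are illustrative; the protocol gives none. In the step 1 formula, ρ of 0.5, 0.6 and 0.7 needs 40, 44 and 49 per group, so a low ρ gives a smaller n. In the T1 comparison adjusted for T0, power at 33 per group is 58% at ρ 0.35, 65% at 0.5 and 81% at 0.7. In the role model (Follow-up as its own level) it is 63%, 70% and 86%. There a low ρ gives lower power.

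**The case against.** The strongest reply is that the protocol nowhere names Implementer versus Waitlist as its main comparison. Section 3.4 refers to differences among three groups, the pairwise tests in section 3.9 are post hoc, both Observer and Waitlist are called control conditions, and the research questions in the Introduction concern change over time, Group 1 at T1 and T2, and all groups at T3. This stands. A reader might infer that the trial as a whole, or its designated primary contrast, is underpowered; the documents do not support that. Implementer versus Observer exceeds 80% even at the Bonferroni level, and so does the overall role test under one effect pattern. But section 3.4 attaches 80% to differences among the three groups without naming a pattern, and under two plausible patterns the overall test also falls well short.

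A second tempting reading is that ρ = 0.35 was an optimistic choice. That is true only inside the formula apparently used. In the planned baseline-adjusted analysis a low ρ lowers power, so it is the cautious direction.

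Third, the formula is inferred and should not be reported as fact. The shortfall does not depend on it: steps 3 to 5 use only the stated inputs and the design.

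Fourth, all randomised participants are to be analysed under intention to treat, so 33 may be too few. Allowing 36 raises Implementer versus Waitlist only to 65–68%. Finally, section 3.4 does not claim to power the Bonferroni-corrected comparisons; those figures are extra information, and the shortfall is already present at 0.05.

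**Conclusion.** The point holds as a mis-stated power figure. With 33 analysed per group, δ 0.50, ρ 0.35 and a two-sided 0.05 level, no coding of the planned role analysis with T0 as a covariate reaches 80% for Implementer versus Waitlist. The range is about 58–65%, or 41–48% at the Bonferroni level by the formulas, and 80% power needs about 0.60–0.65 SD. The overall role test delivers 80% only if Observer is close to Waitlist. The figures rest on exchangeable correlation and normal approximation; a true ρ near 0.7 would bring Implementer versus Waitlist above 80% at the 0.05 level. This is not a finding that the trial is futile or that 110 is the wrong target.

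**What to change.** Keep 110. Rewrite the power paragraph of section 3.4 as follows:

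- Replace the single 80% statement with power by contrast (Implementer versus Waitlist, Implementer versus Observer) and, for the overall role test, by effect pattern. Compute it for the actual role-by-period layout with T0 as a covariate, at 0.05 and at the Bonferroni level, and include the lower Implementer-versus-Waitlist figure.
- Name the function and the layout that produced 33.
- Say which calculation the word conservative refers to, since a low ρ works in opposite directions in the two.

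The cost is one rewritten paragraph and a less favourable stated power for one comparison. No participants, visits or analyses are added.
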